### Data collection, management and analysis

#### Data collection methods

Data will be collected on paper case report forms (CRFs), before subsequent entry into an online database. Semi-structured interviews will be recorded on a Dictaphone before being transcribed verbatim prior to subsequent analysis. MRI data will be stored on the secure CUBRIC database and downloaded on to secure Cardiff University user accounts to enable further processing and statistical analysis.

#### Data management

Electronic data will be stored within firewall- and password-protected computer systems. No data, whether paper or electronic, will leave the Cardiff University site without being completely anonymised. At the conclusion of the study, patient identifiable data will be destroyed and non-identifiable data will be archived for 15 years, in line with Cardiff University policies. Anonymised data may be shared with researchers at Cardiff University and with other research organisations in the UK; it may also be made publicly available for future research use or shared with the organisations who are funding the study. In the case of the data generated using HappyNeuron systems, these data are captured centrally and are therefore subject to HappyNeuron’s policies and procedures. All participant identification and referral procedures as well as procedures for data storage, processing and management will comply with the Data Protection Act 1998. Data collected on paper forms will be stored in locked cabinets in a swipe card access-controlled building, in compliance with the guidelines set by the Cardiff University Research Governance Framework.

#### Statistical methods

Adherence to the proposed cognitive training intervention and any serious adverse events (SAEs) will be reported alongside participant withdrawals. Summary statistics of demographics will be reported for both the control and intervention groups. Descriptive data will include an evaluation of eligibility, recruitment, retention rates and adherence to the intervention, with 95% confidence intervals. Successful adherence to the intervention will be defined as having completed 12 weeks of the computerised cognitive training for a minimum of three, 30-min sessions per week. This is a feasibility study; thus, an estimation of retention rates may be difficult with such as small sample size. Therefore, it is suggested that if retention rates are greater than 75%, we will consider this intervention to be feasible. If the proportion retained is less than this but greater than 65%, we will consider adjusting the intervention to increase this in future investigations.

#### MRI analysis

Potential cognitive training-related changes in the microstructure of white matter pathways of the basal ganglia and motor systems will be assessed with quantitative metrics based on diffusion-weighted (fractional anisotropy, mean and radial diffusivity) and magnetization transfer-weighted MRI (macromolecular proton fraction as proxy MRI metric of axon myelin) [35–37]. Changes in basal ganglia volume will be investigated by extracting subcortical volumes with the FSL-FIRST pipeline [38]. Changes in cerebral blood flow will also be investigated across the whole brain as well as subcortical basal ganglia regions using established methods [39]. The quantitative metrics of tissue structure and blood flow will be correlated with changes in cognition to investigate training-related brain-function associations as well as measures of disease severity, including CAG repeat length, disease burden and Unified Huntington’s Disease Rating Scale (UHDRS) motor scores, using data previously collected and stored as part of the Enroll-HD study.

#### Semi-structured interview analyses

Interview topics will differ slightly depending on allocation and are likely to include how the intervention is perceived/ received, expected or perceived impact on daily routine, expected or perceived impact on family members/carers, overall expectations, expected or perceived acceptability of the intervention, thoughts and views on the randomisation procedure, potential barriers to completing the intervention and general views or comments on cognitive training for people impacted by HD.

Interviews will be transcribed verbatim and analysed using thematic analysis [40]. The data set will be searched to find repeated patterns of meaning, identifying key themes and sub-themes. We will identify contradictory data, as points of contrast as well as similarities in order to understand uptake and engagement with the intervention. Double coding will be utilised to ensure data validity, reliability and integrity. Data will be managed using the qualitative coding software NVivo.

### Monitoring

#### Data monitoring

As this is a non-Clinical Trial of an Investigational Medicinal Product (non-CTIMP) feasibility study which is judged to pose minimal risk to participants, it has been judged that there is no formal need for a DMC. However, the Chief Investigator (CI) will produce regular data monitoring reports to the Centre for Trials Research (CTR) advisory board. The board will assess the data quality and monitor this throughout the study.

#### Harms

The safety of the proposed cognitive training intervention will be monitored throughout the feasibility study by recording of all adverse events (AE). Based on the use of this cognitive intervention programme in a similar patient population with other neurodegenerative diseases [24], we do not anticipate any serious adverse events (SAEs) related to the intervention. However, safety will be monitored throughout and any AEs or SAEs will be recorded using a standard template and reported in line with standard operating procedures and research ethics committee requirements. If, in the opinion of the CI, the SAE was related to the administration of any of the research procedures and was an unexpected occurrence, the CI will report this to the REC within 15 days of becoming aware of the event. If the clinician responsible for the clinical care of participants deems that it is clinically necessary to stop the intervention, the participant will be withdrawn from the intervention. However, the participant will still be invited to complete the outcome assessments. Relapse, worsening of symptoms of HD, death due to HD and hospitalisations for elective treatment of a pre-existing condition will not be reported as SAEs.

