## Background

### Background and rationale

Huntington’s disease (HD) is caused by a CAG repeat trinucleotide expansion within the first exon of the *huntingtin* gene [1], and it causes a range of symptoms including motor, cognitive and psychiatric disturbances [2–8]. These disease symptoms significantly affect daily activities, independence and quality of life, even during the early stages of the disease [9, 10]. Cognitive dysfunctions early in the HD disease process have been well documented and can include specific problems with attention, cognitive flexibility and memory [11, 12]. Therefore, cognitive training interventions, which focus on tasks that require executive function, present a potentially exciting non-pharmacological treatment option for neurodegenerative diseases including HD. Studies in HD mice have previously demonstrated executive function impairments [13, 14], and subsequent studies have shown that cognitive training can benefit HD mice and modify the associated cognitive and motor disease symptoms [15, 16]. These results provide important ‘proof of principle’ evidence that an early cognitive training intervention may be beneficial in HD.

Furthermore, there is accumulating evidence in both healthy and clinical populations that cognitive training, via repeatedly conducting tasks that require specific aspects of executive function such as attention, reasoning, dual tasking and memory, can improve cognitive functions in the trained domain [17–20]. For instance, computerised cognitive training on such tasks has been found to improve cognitive impairments in Alzheimer’s disease [21–23] and Parkinson’s disease [24–26]. In addition, a recent single arm feasibility study demonstrated the feasibility of and adherence to working memory training on the Cogmed QM programme in a small sample of HD patients [27]. Furthermore, previous studies have found that training-related changes are associated with alterations in white matter, particularly with regard to altered myelination in both healthy controls [28] and HD [20]. Thus, we intend to use MRI measures to explore the potential neural mechanisms which may be associated with computerised cognitive training in the HD clinical population.

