#### Blinding (masking)

Blinding is not used in this study, due to limited resources and staffing. Participants allocated to the intervention group will know that they have been allocated to this group as they are required to complete the cognitive training intervention. The lack of blinding is a limitation of the study design; however, quantitative outcome measures have been utilised where possible in order to minimise the possible bias that may be introduced due to a lack of blinding.

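### HD worsening and HD-attributed deaths are kept out of the SAEs without exception, and the statistical methods name only SAEs and withdrawals as harms to report, so these events need not appear in the harms summary

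*Protocol article*

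**What the plan says.** Four statements in the protocol article bear on this.

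- **Collection (Harms).** Safety is "monitored throughout the feasibility study by recording of all adverse events". The section adds that "any AEs or SAEs will be recorded using a standard template and reported in line with standard operating procedures and research ethics committee requirements".
- **Exclusion (Harms, last sentence).** Along with relapse, "worsening of symptoms of HD, death due to HD and hospitalisations for elective treatment of a pre-existing condition will not be reported as SAEs". The rule has no qualification by relatedness, severity or route of reporting.
- **Results (Statistical methods).** Adherence is to be given and "any serious adverse events (SAEs) will be reported alongside participant withdrawals". Adverse events that are not SAEs are not mentioned there.
- **Blinding (Blinding section).** "Blinding is not used in this study, due to limited resources and staffing".

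The Harms section also has a separate route to the ethics committee, with a 15-day limit, for an unexpected event where "in the opinion of the CI, the SAE was related to the administration of any of the research procedures". The Data monitoring section says that no DMC is needed and gives the advisory board the task of assessing data quality.

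**The concern.** Excusing expected disease events from expedited reporting is common and defensible. Leaving them out of the trial's results is a different decision, and the article does not separate the two. The exclusion says these events are not reported as SAEs, and the results section then names SAEs as the adverse events to be reported.

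The excluded class may be wide. The Background says of HD that "it causes a range of symptoms including motor, cognitive and psychiatric disturbances". That sentence is not an operational definition of worsening, but it shows that a motor, cognitive or psychiatric deterioration during training could readily be classed as disease.

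A randomised control arm makes it possible to separate disease progression from an effect of the intervention without judging each case. An exclusion based on case-by-case attribution gives up that advantage, and here the attribution is made with allocation known. The Discussion says that the data will inform larger trials, so the harms summary is one of the things that those trials will inherit.

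**Working it through.** There is no stated figure to reproduce. The check sets the sections side by side and then shows what the exclusion does to a count.

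**1. Path of a serious event attributed to HD.**

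| Step | Section | Result |
|---|---|---|
| Is it recorded? | Harms | Yes, as an adverse event |
| Is it reported as an SAE? | Harms, last sentence | No, with no exception for a possible link to training |
| Does it reach the CI's relatedness judgement? | Harms | Read literally, no: that step applies to an SAE |
| Is it in the harms named for the results? | Statistical methods | Not as an SAE; only indirectly if the participant also withdraws |

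The event is therefore on file, but nothing in the article requires it to be shown in the results.

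**2. Effect on a comparison by arm.** Let s be the number of serious events in an arm and h the number of those attributed to excluded HD categories, with h between 0 and s. The SAE summary shows s − h. The difference between the arms (T training, C control) becomes

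(s_T − h_T) − (s_C − h_C) = (s_T − s_C) − (h_T − h_C).

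- If the same fraction p of serious events is attributed to HD in both arms, the reported difference is (1 − p) times the true one. It shrinks towards zero, and reaches zero when p = 1.
- If attribution depends on knowledge of the arm, h_T − h_C can distort the difference in either direction. The article gives no basis for saying which.

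**3. Scale.** The Sample size section targets 40 randomised participants. Assuming an equal split, which the article does not state for the whole sample, each arm has 40 / 2 = 20. One participant left out changes an arm's proportion by 1 / 20 = 5 percentage points. The article gives no rate of serious HD worsening or of death over 12 weeks, so h could be zero, and the expected number of affected events cannot be derived.

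**The case against.** The strongest reply is that the exclusion belongs to reporting procedure. It closes a paragraph about recording and ethics committee reporting, and may mean only that expected disease events are not processed as SAEs. The full protocol or an analysis plan, neither of which is shown, could hold a complete adverse event table. That is a possible reading, but the sentence does not limit itself to the expedited route, which has already been described separately. A later table of SAEs would also inherit the definition. The point challenges a rule that is stated, not a detail that is absent.

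Several stronger readings are tempting and are not supported.

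- **That the trial could not show such harms by arm.** All adverse events are recorded, so the data for a table by arm should exist. Group effect estimates are a secondary objective, and cognitive, motor and questionnaire outcomes are collected. The abbreviations list includes an anxiety and depression scale and timed up and go tests. Participants taken off the intervention by a clinician are still invited to assessments, and withdrawals and retention are reported. Part of any worsening would show there. This does not replace a count of serious events: a participant who dies has no later score, an invited participant may not attend, and withdrawal may be without reason.
- **That only SAEs will ever be reported.** The Statistical methods section names SAEs and withdrawals but does not say that nothing else will follow, and the Harms section refers to reporting AEs under standard procedures.
- **That HD worsening is the most plausible harm of the training.** The article does not say so. It anticipates no related SAEs and judges the risk to be minimal.
- **That a report of no SAEs would be true by definition.** Deaths not due to HD, and unplanned hospitalisations not due to HD worsening, stay within the SAEs.
- **That a named unblinded person decides what counts as HD worsening.** The article does not say who decides. What stands is that nothing is blinded and no blinded assessor of events is described.

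**Conclusion.** The point holds in a limited form. As written, serious worsening of HD and deaths attributed to HD need not appear in the only harms summary that the article specifies, even if they might be related to the training, and the attribution that removes them is made without blinding. The data are not lost; the defect lies in what the plan commits to showing.

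The size cannot be stated as a number of events. Under equal allocation, each omitted participant is worth 5 percentage points in an arm. Under attribution that is the same in both arms, the reported difference shrinks in proportion to the share of events excluded.

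This rests on two assumptions: that the exclusion is applied as worded, and that the results follow the Statistical methods section. It does not affect the recruitment, retention or adherence estimates. It should be corrected, because the trial is meant to inform larger ones and the correction is cheap.

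**What to change.** 1. In Statistical methods, replace the reference to SAEs with a commitment to report all recorded AEs and SAEs by arm. Include worsening of HD symptoms, deaths from any cause and all hospitalisations, regardless of attribution. Attribution can be shown as an extra column.
2. In Harms, if the exclusion is meant to apply to expedited reporting to the ethics committee, say so, and state that it does not govern the results.
3. Reconcile the two sections so that one definition of what is reported serves both.

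The cost is a few sentences and one descriptive table. The events are already to be recorded on the standard template, so no new data collection is needed, and clinical management is unchanged. With so few participants the table should be descriptive, with counts of participants and events and no tests.

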#### MRI and incidental findings

MRI scanning at 3 Tesla is a well-established and non-invasive technique for imaging the body and the brain using strong magnetic fields and low-energy radio waves. It does not involve the use of radiation. All persons entering the scanning room are screened for ferromagnetic materials or other factors which cause risk in the presence of a strong magnetic field. The scanner creates significant noise during the scan, which is minimised using earplugs. Verbal contact will be maintained between the MRI operators and the participant through the use of intercom, and a call button will be given to the participant to enable them to stop the scanning procedure at any time. A few people have reported minor side effects during MRI scanning including dizziness, mild nausea, a metallic taste in the mouth, peripheral nerve stimulation and the sensation of seeing flashing lights. These side effects, if experienced, resolve after leaving the magnet, and participants will be informed in the participant information sheet (PIS) of the MRI scanning session of these rare side effects. Some people find being inside an MR scanner claustrophobic; thus, in addition to the 3 Tesla MR machine, CUBRIC also has a ‘mock’ scanner that reproduces, as far as possible, the look and feel of the real MR machine, but without the presence of a magnetic field. Participants will be given the opportunity to lie in this ‘mock’ scanner to acclimatise in advance of the real MRI scan session. If the participant finds the experience in either scanner unpleasant, then he/she would be removed from the scanner.

In some circumstances, changes in the magnetic field within the MRI scanner could make an electric current flow through some of the volunteer’s body, causing peripheral nerve stimulation; this is very rare for the 3 Tesla MRI scanner and not harmful but may be uncomfortable. If two parts of the volunteer’s body were touching (for instance legs crossed), then in very rare occasions, it is possible that an induced current may cause skin heating. Volunteers are instructed to lie with their arms to their sides and legs uncrossed, which stops this from happening. Participants will be informed that CUBRIC is a research centre and therefore cannot provide clinical diagnoses; acquired images of the brain are used for specific research purposes only and not suitable for diagnosis of pathology. However, although the pictures are not diagnostic scans, in the unlikely event of a structural abnormality being noted incidentally, a neuro-radiologist would be asked to review the scan and the clinical lead of the study will be informed. The participant’s general practitioner (GP) will then be notified by the neurologist. There may be a need for the GP to arrange for a formal diagnostic scan.

#### Auditing

The study is subject to inspection by The Jacque and Gloria Gossweiler Foundation and Health and Care Research Wales as the funding organisations. The study may also be subject to inspection and audit by Cardiff University under their remit as sponsor.

#### Consent

Potential participants will be given as long as they need to read the PIS, consider the study and discuss it with the researchers or friends or family, as required. Informed consent will then be obtained by means of a participant dated signature and a dated signature of the person who obtained the informed consent. Participants will be asked during the consent process if their family member, friend or carer can be asked their opinions of cognitive training interventions. If participant consent is provided to ask family members, friends or carers for their opinions, they will be asked to read a separate participant information sheet (PIS) and provide their consent by means of a dated signature and a dated signature of the person who obtained the informed consent. The friend or family member will then be asked to complete a semi-structured interview similar to that described above.

#### Confidentiality

All participant identification and referral procedures as well as procedures for data storage, processing and management will comply with the Data Protection Act 1998. Data will be kept for 15 years in line with Cardiff University’s Research Governance Framework Regulations for clinical research. This data will be stored confidentially on password protected servers maintained on the Cardiff University Network. Data collected on paper forms will be stored in locked cabinets, and electronic data will be stored on secured computer hard drives (password protected) in a swipe card access-controlled building, in compliance with the guidelines set by the Cardiff University Research Governance Framework. The confidentiality of participants will be preserved in accordance with the Data Protection Act 1998. All participants will be allocated a unique study number identifier, and in the case of family members, friends or carers, they will be allocated a unique study number in relation to the participant. All data collected will be held in a linked anonymised form.

#### Dissemination policy

The research team are committed to disseminating the research findings to the general public and to patient groups; therefore, we will seek to present the results at patient open days, engagement events and outreach activities. Furthermore, in order to communicate the research widely, the results may be disseminated via social media, through newsletters and other patient engagement outlets in appropriate language and format for the general public to understand. If a participant indicates that they would like to be informed of the results of the study, a report of the findings will be sent to them at study closure. Where results are presented, they will always be presented in such a way that data from individual participants cannot be identified. In addition to the significant public and patient outreach dissemination, the research findings will be written up for publication in a scientific journal. The results may also be presented at scientific meetings, academic institutions or as part of public engagement and outreach events.

#### Protocol version and amendments

This publication is based on protocol version 4.0 _31.07.2017. The protocol has been written in line with both the CONSORT (Consolidated Standards of Reporting Trials) statement [41] and SPIRIT (Standard Protocol Items: Recommendations for Interventional Trials) guidelines [42]. Any updated protocols will be communicated to the study team via email and telephone as appropriate.

